### Imaging and statistical analysis

Atherosclerotic plaques in both carotid arteries (ipsilateral and contralateral to the ischemic stroke) will be recorded and classified according to the modified criteria of the American Heart Association [14]. Tissue components (necrotic core, calcification, hemorrhage, loose matrix) and type and location of hemorrhage will be identified and quantified based on previously published criteria [15,36]. For definition of a complicated AHA-LT-VI plaque, at least one of the following three criteria is required: fibrous cap rupture, intraplaque hemorrhage, juxtaluminal hemorrhage/mural thrombus (see Figure 1 for an example of a complicated AHA-LT VI). Area measurements of the lumen, outer wall, and tissue components are obtained using the custom-designed image analysis tool CASCADE (University of Washington, Seattle, US) [37].

**Figure 1 F1:**
[figure not shown]
**Axial images of specific AHA-LT VI plaque features in a patient with acute ischemic infarct.** High-resolution black blood MRI of the carotid arteries demonstrate a large eccentric plaque with <50% stenosis in the right carotid artery, hyperintense on T1w, T2w and PDw sequences consistent with fresh intraplaque hemorrhage (**A**, arrow). Axial images 0.6 cm above the bifurcation show an area attached to the plaque, which is hypo- to isointense on T1w + CM, PDw and TOF, consistent with a mural thrombus (**B**, arrow). (T1w: T1-weighted black blood sequence, PDw: PD-weighted sequences, T2w: T2-weighted sequence, TOF: Time-of-flight MR angiography, T1w + CM: T1-weighted black blood sequence after contrast administration).

All carotid and brain MRI examinations will be evaluated by two radiologists blinded to the clinical status. In case of discordant results, a consensus decision will be made. Image quality is rated on a five point scale (1 = worst, 5 = best), with MRIs ≥3 included for further analysis [31].

New ischemic lesions on brain MRI during follow up are defined as hyperintense lesions clearly visible on T2 weighted sequences.

All statistical analyses will be performed using SPSS and SAS. For determination of differences in prevalence of complicated AHA-LT VI plaques between patients with cryptogenic stroke and stroke with defined etiology the Chi square test will be used. Differences in the prevalence of complicated AHA-LT VI plaques ipsi- and contralateral to the ischemic stroke will be calculated using the McNemar Test. For the cross-sectional analysis the prevalence of AHA-LT VI plaques in patients with territorial infarcts, multiple embolic infarcts and small lacunar lesions will be compared. Furthermore, the difference in prevalence of AHA-LT VI plaques in patients with aortic arch plaques < 3 mm and > 3 mm will be determined. Data from the serial plaque study are analyzed in accordance to previous studies [38]. The effect of plaque morphology on cerebrovascular (TIA, amaurosis fugax and stroke) and cardiovascular events (myocardial infarction, vascular death) will be assessed using Cox proportional-hazards regression analysis. Cohen’s kappa test will be employed to evaluate the intra- and inter-reader agreement for identification of AHA-LT VI.

For distinctions of the stroke subtypes regarding recurrence rates of cerebrovascular events, Kaplan-Meier curves and Cox regression analysis will be used. For categorical variables, Fisher’s exact test and for continuous variables, an unpaired t-test will be applied. All p-values <0.05 will be considered as statistically significant.

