### Patient population - Inclusion and exclusion criteria

Patients of both genders older than 49 years presenting with neurological symptoms compatible with an acute unilateral anterior circulation infarct within the last seven days are recruited through certified stroke units at the participating centers. DWI positive lesions in the territory of a single internal carotid artery (ICA) on cerebral MRI and the presence of plaques with ≥ 2 mm thickness on one of the carotid arteries as defined by ultrasound are required for inclusion. Patients with high-grade carotid artery stenosis (≥70% NASCET) are excluded from the study as these patients usually undergo immediate invasive treatment (carotid endarterectomy or carotid artery stenting) following current guidelines. Additional exclusion criteria include bilateral ischemic lesions and infarcts within the posterior circulation. For detailed inclusion and exclusion criteria see Table 1.

**Table 1 T1:** Inclusion and exclusion criteria

**Inclusion criteria**	**Exclusion criteria**
• Age > 49 years old	• Primary referral to an outside hospital
• Acute ischemic stroke or transient ischemic attack (TIA)	• DWI positive lesions outside the territory of a single internal carotid artery
• Neurological symptoms compatible with a stroke or TIA in the territory of the internal carotid artery	• Surgical procedure within 24 hours preceding the MRI
• Onset of symptoms within the last 7 days	• History of radiation to the neck area
• 1 or more acute ischemic lesion(s) visible on MR diffusion-weighted imaging (DWI) in the territory of a single internal carotid artery	• Carotid artery stenosis ≥70% (NASCET) ipsilateral to the stroke or TIA as defined by ultrasound (systolic peak flow velocity ≥ 300 cm/s)
• Presence of carotid artery plaques in the ipsi- or contra-lateral carotid artery as defined by ultrasound (plaque thickness at least 2 mm; located within 1 cm proximal or distal to the carotid bifurcation)	• Creatinine levels > 2 times the upper limit of the standard range of the respective laboratory within the last 30 days prior to MRI and Renal clearance < 30 ml/minute
• Written informed consent	• Standard contra-indications for MRI

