### Secondary outcomes

Secondary outcomes include the association of complicated AHA-LT VI plaques with specific infarct patterns (territorial infarcts, multiple embolic infarcts, small lacunar lesions), with aortic arch plaques as determined by transoesophageal echocardiography or computed tomography angiography (CTA) and their association with biomarkers derived from serum and plasma. Furthermore, we will evaluate the recurrence rate of ischemic events and the rate of new ischemic lesions on brain MRI in patients with complicated AHA-LT VI plaques after twelve months follow up. In addition, we will investigate whether specific features of complicated AHA-LT VI plaques, such as intraplaque hemorrhage and thin or ruptured fibrous cap are associated with an increased progression rate of atherosclerotic disease burden after twelve months.

Recurrent ischemic events include cerebrovascular and cardiovascular events. Cerebrovascular events are defined either clinically (TIA, amaurosis fugax or stroke), by brain MRI alone (new ischemic lesion on brain MRI) or on the combined assessment of clinical findings and brain MRI. Furthermore, the most likely cause of the recurrent cerebrovascular event is classified according to the ASCO and TOAST classifications. Unilateral events in the anterior circulation will be included in the final analysis to estimate the risk of recurrent events in patients with AHA-LT VI plaques. Recurrent ischemic events in other territories, bilateral events and cardiovascular events (myocardial infarction, vascular death) are recorded during follow-up to evaluate if patients with complicated AHA-LT VI plaques have a higher overall atherosclerotic disease burden.

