### Assessment

All patients included into the study are interviewed and examined within 7 days after stroke onset. Assessment at 3, 24 and 36 months follow up is performed using a structured telephone interview conducted centrally by the coordinating center (LMU Munich). Twelve month follow up consists of a clinical examination by a stroke neurologist, blood investigations as well as repeated carotid and brain MRI. Table 2 gives a detailed schedule of planned assessments and time points. In cases where no contact with the patient can be established, information will be obtained from the Residents’ Registration Office.

**Table 2 T2:** Schedule of assessments

**Month**		**0**	**3**	**12**	**24**	**36**
Informed consent		X				

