#### *Brain MRI*

Unilateral infarct localization within the anterior circulation is confirmed by brain MRI. Infarcts are defined as acute diffusion restrictions (hyperintensities) on Diffusion weighted images with corresponding hypointense areas on ADC maps. In addition T2-weighted and FLAIR sequences are acquired.

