## Discussion

This study differs from previous carotid plaque imaging studies in several ways. First, we focus on patients with cryptogenic stroke, classified by two raters and exclude patients with high grade stenosis (>70%), who usually undergo immediate invasive treatment and cannot be followed regarding plaque progression. Second, most previous studies have used a broader definition of the index event, including not only patients with a stroke documented by DWI-positive lesions on brain MRI, but also patients with TIA and amaurosis fugax [16,19], or even focused on asymptomatic patients [20,22]. Third, the time interval between the event and the MRI scan was up to 3 months [23], whereas CAPIAS includes patients within 7 days after symptom onset. Histopathological studies have shown that plaque features associated with vulnerability have the highest frequency in the first days after the ischemic event, thus suggesting that a short time period between event and MRI seems to be preferable [6,39]. Furthermore we excluded stroke patients younger than 50 years because the etiologic spectrum in this group differs from that in older subjects. The most frequent etiologic subgroups in the age range of 16–49 years are cardioembolism and arterial dissections while strokes due to large-artery atherosclerosis are extremely rare [40]. Finally, patients are systematically followed by clinical examination for 36 months and brain MRI for 12 months. Recent results of relatively small studies suggested that with improvement in best medical treatment the rate of recurrent events has decreased substantially in recent years. However, to date no larger trials are available which show the exact rate of recurrent events in ischemic stroke patients with <70% carotid artery stenosis and >2 mm atherosclerotic plaques and therefore it is impossible to provide precise estimates of the rate of stroke recurrence. In order to improve the power of the study we will use a clinical follow up period of 36 months and we will count silent ischemic lesions in the 12 months follow up brain MRI. Furthermore we will collect the number of TIA, amaurosis fugax and cardiovascular events.

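### New ischemic lesions at 12 months are defined by T2 visibility alone, which cannot separate a new infarct from white-matter change or from evolution of the index infarct

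*Protocol article*

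**What the plan says.** The only operational definition is in the protocol article, Imaging and statistical analysis (the text after Figure 1): "New ischemic lesions on brain MRI during follow up are defined as hyperintense lesions clearly visible on T2 weighted sequences".

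The surrounding text bears on it as follows.

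- **Baseline imaging.** Under Brain MRI, the acute infarct has a two-part definition: "Infarcts are defined as acute diffusion restrictions (hyperintensities) on Diffusion weighted images with corresponding hypointense areas on ADC maps". The section adds: "In addition T2-weighted and FLAIR sequences are acquired". A baseline comparator therefore exists.
- **Index lesion.** Table 1 requires of every patient: "1 or more acute ischemic lesion(s) visible on MR diffusion-weighted imaging (DWI) in the territory of a single internal carotid artery".
- **Follow-up imaging.** Under Assessment: "Twelve month follow up consists of a clinical examination by a stroke neurologist, blood investigations as well as repeated carotid and brain MRI". Table 2 schedules cerebral MRI at months 0 and 12 only.
- **Use as an event.** Secondary outcomes allows a cerebrovascular event to be defined "by brain MRI alone (new ischemic lesion on brain MRI"). It then restricts the main recurrence analysis: "Unilateral events in the anterior circulation will be included in the final analysis".
- **Purpose.** In the Discussion, to improve power, "we will count silent ischemic lesions in the 12 months follow up brain MRI".
- **Cox model.** In Imaging and statistical analysis, the model for plaque morphology lists TIA, amaurosis fugax, stroke, myocardial infarction and vascular death. MRI-only lesions are not in that list.

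**The concern.** The rule rests on a single sign, and that sign is not specific to infarction. It does not state that the lesion must be absent at baseline or lie outside the index lesion, and it gives no way to tell an infarct from white-matter change. The baseline infarct, by contrast, needs both a DWI and an ADC finding.

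The cohort is exposed to this weakness. Every patient has an index infarct, imaged early, whose T2 extent may change afterwards. The restriction to unilateral anterior-circulation events does not help, because the index infarct lies in that territory. Among the first 79 patients (Table 3), median age was 74, 72% had hypertension and 13% had small vessel occlusion, so new or enlarging white-matter hyperintensity over a year is plausible.

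At stake are two secondary results: the rate of new MRI lesions, and recurrence where an MRI finding alone qualifies. True events are expected to be few, so a modest number of false ones could outweigh them. A step taken to raise power could then lower it.

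**Working it through.** **Nearest stated figure.** No published number rests on the lesion definition. The closest is the claim under Sample size that 300 patients suffice for recurrence, given 8% at 12 months and a hazard ratio (HR) of at least 5.

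- Expected events: 300 × 0.08 = 24.
- Events needed (Schoenfeld), with two-sided 5%, 80% power and 30% plaque prevalence all assumed, since the section gives none of them for this outcome: (1.96 + 0.84)² / (0.3 × 0.7 × (ln 5)²) = 7.85 / 0.544 = 14.4, so 15.
- At prevalences of 10%, 20% and 40% the requirement is 34, 19 and 13. The claim therefore holds at 20% to 40% prevalence, but not at 10%.

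**Inputs for the illustration.**

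- From the document: n = 300, overall 12-month risk 8%, HR 5.
- Assumed: plaque prevalence 30% (90 and 210 patients), and a share f of patients falsely scored as having a new lesion, independent of plaque status. The document gives no value for f.

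**Step 1, true risks.** Find h such that 0.3(1 − e^(−5h)) + 0.7(1 − e^(−h)) = 0.08. This gives h = 0.0390, so the risk is 17.7% with AHA-LT VI plaque and 3.8% without.

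**Step 2, observed risks.** Observed risk = 1 − (1 − r)(1 − f). For f = 10%: 1 − 0.823 × 0.9 = 26.0% and 1 − 0.962 × 0.9 = 13.4%.

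**Step 3, observed HR.** HR = [5h − ln(1 − f)] / [h − ln(1 − f)]. For f = 10%: (0.195 + 0.105) / (0.039 + 0.105) = 2.1.

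**Step 4, counted events.** 300 × [1 − 0.92(1 − f)]. For f = 10%: 300 × 0.172 = 52, of which 24 (47%) are true.

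**Step 5, power.** Two-proportion normal approximation, 90 v 210, two-sided 5%, pooled variance under the null.

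| f | Observed risk, with v without plaque | Counted events | True share | Observed HR | Power |
|---|---|---|---|---|---|
| 0% | 17.7% v 3.8% | 24 | 100% | 5.0 | 96% |
| 5% | 21.8% v 8.6% | 38 | 63% | 2.7 | 85% |
| 10% | 26.0% v 13.4% | 52 | 47% | 2.1 | 73% |
| 20% | 34.2% v 23.1% | 79 | 30% | 1.6 | 52% |
| 30% | 42.4% v 32.7% | 107 | 22% | 1.4 | 37% |

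**Sensitivity to prevalence.** At f = 10%, prevalences of 20% and 40% give an HR of 2.25 and 1.95, and power of 75% and 67%.

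**Direction.** The table covers only false positives unrelated to plaque. If they are more frequent in patients with AHA-LT VI plaques through shared vascular risk, the observed ratio could be inflated instead.

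**The case against.** The strongest reply is that the sentence defines new lesions during follow-up, that brain MRI is done at months 0 and 12, and that T2 and FLAIR exist at baseline. On the natural reading, T2 is simply how a lesion acquired in the interval is recognised at 12 months. An old scar is not new.

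Much of this stands. A reader might infer from the bare rule that every index scar and old white-matter lesion will be scored as a recurrence, so that up to 300 of 300 patients have an event. The document does not support that: radiologists would have to ignore the word new and the baseline scan. A baseline comparison was probably intended and would remove most stable scars and old lesions. It would not resolve the remaining cases, which are white-matter hyperintensity that appears or grows in the interval and an index infarct whose T2 extent changes. Both can differ from baseline without a new infarct.

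A second reply is that minimum size and white-matter rules belong in an imaging manual, and that a condensed article may omit them. That is fair for detail. But the article does state a definition, and its one criterion is not specific to infarction.

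Third, there are safeguards: two radiologists blinded to clinical status, consensus reading, an image-quality threshold, and classification of recurrent events by raters blinded to carotid MRI. These limit reader-driven bias by plaque status. They do not make a non-specific criterion specific, and kappa is planned only for AHA-LT VI.

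Fourth, the Cox model for plaque morphology lists clinical events only. That stands and narrows the point. As worded, that model is untouched, but its list differs from the event definition in Secondary outcomes and from the stated wish to gain power from silent lesions.

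**Conclusion.** The concern holds in a limited form. The stated rule implies a baseline comparison without requiring it. Even with one, it cannot separate a new infarct from new or enlarging white-matter hyperintensity or from T2 evolution of the index infarct.

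The effect is confined to the secondary new-lesion rate and to recurrence as Secondary outcomes defines it. Plaque prevalence, the primary outcome, is not affected, nor is the plaque-morphology Cox model as worded.

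The size is illustrative. With only 24 true events expected, a false-positive share of 10% would leave fewer than half of the counted events true and cut an HR of 5 to about 2. These figures depend on the assumed share, the assumed 30% prevalence, and false positives that are unrelated to plaque. The document supports no particular share, and the direction of bias is not certain. The point is worth correcting because the correction is cheap, but it does not threaten the study's main result.

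**What to change.** Replace the sentence with a full reading rule. A new ischemic lesion is a T2/FLAIR hyperintensity at 12 months that:

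- is absent on the baseline DWI, T2 and FLAIR images in a side-by-side reading;
- lies outside the baseline DWI lesion;
- meets a prespecified minimum size (3 mm is one option; the document implies no particular value);
- is not confluent or periventricular white-matter change, under a prespecified rule.

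Record the side of each new lesion relative to the plaque.

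Also reconcile Secondary outcomes, Imaging and statistical analysis, and the Discussion on whether MRI-only lesions enter the time-to-event analysis or are reported only as a separate 12-month rate.

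The cost is slightly more reading time for the same two radiologists, on baseline sequences the protocol already acquires, and a somewhat lower lesion count.

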In our study “Cryptogenic stroke” is defined as a stroke `of undetermined origin’ according to TOAST classification, which is equivalent to the absence of grade 1 pathology according to A-S-C-O. Thus, patients with concurrent etiologies will be analyzed as a separate group. Patients with cardioembolic stroke or small vessel disease represent the negative control group and patients with large artery atherosclerosis (50-69% stenosis) serve as positive control.

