### Primary outcome

The primary outcome of the CAPIAS study is the prevalence of complicated AHA-LT VI plaques ipsilateral to an acute ischemic stroke in the territory of a single carotid artery in patients with a cryptogenic stroke. The analyses will include a comparison of the prevalence of complicated AHA-LT VI plaques ipsilateral versus contralateral to the ischemic stroke and a comparison of complicated AHA-LT VI plaques in patients with cryptogenic stroke as compared to patients with defined stroke etiology.

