### Sample size

Based on a pilot study by Freilinger et al. [24], we estimated that 40% of ipsilateral carotid artery plaques in patients with a cryptogenic stroke are complicated AHA-LT VI plaques. Thus, in 100 patients with cryptogenic stroke the prevalence can be assessed with a precision of +/− 10%. Our unpublished pilot data indicate a prevalence of complicated AHA-LT VI plaques in patients with defined stroke etiology of about 10%. To determine this difference with a power of 80% and 5% level of significance, 32 patients of each group (cryptogenic and control group) would be sufficient. Assuming a prevalence of complicated AHA-LT VI plaques of 30% in the cryptogenic stroke group, 64 patients in each group are needed.

The recurrence rate of ischemic stroke associated with complicated AHA-LT VI plaques will be determined as the time period until the next ischemic event. Assuming a recurrence rate of ischemic events of 8% [35] within 12 months following the index stroke and a hazard ratio of AHA-LT VI plaques ≥ 5 [19,34,35], 300 patients will be enough to demonstrate a significant difference in event rates between patients with and without AHA-LT VI plaques.

Previous longitudinal studies, which demonstrated associations of intraplaque hemorrhage with accelerated plaque progression and with new surface disruption, were able to show those associations with much smaller sample sizes [21,36]. Thus 300 patients will provide sufficient power to detect effects of certain plaque features on plaque progression.

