This study also has limitations. Secondary prevention during follow up will differ among study participants depending on previous medication and stroke etiology. Patients with LAA or SVD are treated with antiplatelet agents, whereas patients with a cardioembolic etiology usually receive anticoagulants. Also, this study offers no information on the natural history of carotid plaques as all patients receive statin treatment for secondary stroke prevention. As demonstrated in several studies, statins influence the development of plaque burden, intraplaque hemorrhage and inflammation [39]. Another limitation is the additional scan time of the study-related MRI protocol, which may result in movement artifacts and severely affected stroke patients may refuse receiving an additional MRI.

So far, clinical and radiological baseline data of 79 patients have been analyzed. Stroke subtyping using the TOAST criteria showed the following distribution: 14% of subjects had LAA, 27% had CE, 13% had SVD, 5% had multiple potential causes (MPC) and 40% had cryptogenic stroke (Table 3). The small number of patients with LAA, the absence of other stroke causes and the high percentage of cryptogenic stroke result from our inclusion and exclusion criteria. Thus, the number of patients with LAA is smaller than expected as patients with ≥ 70% stenosis are excluded. Furthermore, we only include patients with advanced atherosclerotic disease, defined as plaques ≥ 2 mm in the carotid arteries, which might also explain the smaller than expected%-ages of patients with CE and SVD and the absence of patient with other stroke causes e.g. carotid artery dissection. Consistent with this notion, patients with cryptogenic stroke compromised almost half of our patient population, suggesting a potential link between atherosclerotic disease and the underlying cause of the ischemic stroke.

**Table 3 T3:** Baseline characteristics of the first 79 patients enrolled in Munich

Age in years (median, Q1-Q3)		74 (68–83)
Female (n,%)		25 (32)
Systolic blood pressure at admission (mean, SD)		142 (19)
Diastolic blood pressure at admission (mean, SD)		78 (11)
BMI (mean, SD)		26 (3)
Pre stroke living condition (n,%)		
	At home alone	23 (32)
	At home with family or friends	46 (64)
	Institutionalized	2 (3)
NIHSS at admission (n,%)		
	0–4	51 (65)
	5–15	24 (30)
	≥16	4 (5)
mRS on admission (n,%)		
	0–2	47 (60)
	3-5	31 (40)
B I on admission (n,%)		
	0–19	5 (6)
	20–49	15 (19)
	50–74	6 (8)
	75–99	16 (20)

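### The between-group Chi-square test, as written, pools the positive control (large artery atherosclerosis) with the negative controls, which dilutes the contrast and ties it to case mix

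*Protocol article*

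**What the plan says.** All places are in the Protocol article.

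- **Patient population:** CE and SVD form the negative control group, while "patients with large artery atherosclerosis (50-69% stenosis) serve as positive control". Patients with concurrent etiologies are set apart as their own group.
- **Primary outcome:** the outcome is the ipsilateral prevalence in cryptogenic stroke. The analyses include an ipsilateral-contralateral comparison and "a comparison of complicated AHA-LT VI plaques in patients with cryptogenic stroke as compared to patients with defined stroke etiology".
- **Sample size:** for cryptogenic stroke, "we estimated that 40% of ipsilateral carotid artery plaques in patients with a cryptogenic stroke are complicated AHA-LT VI plaques". For the comparator, "Our unpublished pilot data indicate a prevalence of complicated AHA-LT VI plaques in patients with defined stroke etiology of about 10" per cent. This gives 32 per group, and then: "Assuming a prevalence of complicated AHA-LT VI plaques of 30% in the cryptogenic stroke group, 64 patients in each group are needed". The section speaks of a single control group.
- **Imaging and statistical analysis:** "between patients with cryptogenic stroke and stroke with defined etiology the Chi square test will be used".
- **Discussion and Table 3:** among the first 79 patients, "14% of subjects had LAA, 27% had CE, 13% had SVD"; the counts are 11, 21 and 10, with 32 cryptogenic.

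**The concern.** A positive control is included because it is expected to show the lesion, and a negative control because it is not. The article assigns these two roles under Patient population. It then drops the distinction where the comparison is defined, sized and tested. Followed literally, the Chi-square test puts the positive control in the comparator.

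Two things are at stake. First, if LAA has more complicated plaques than CE/SVD, the comparator rate rises and the contrast shrinks for a reason unrelated to cryptogenic stroke. Second, the result depends on how many LAA patients happen to be recruited. A weak contrast could then mean either that the hypothesis is wrong or that the comparator is rich in LAA, and the pooled test cannot tell these apart.

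**Working it through.** **1. The plan's own figures.** Two-sided 5% level (sidedness is not stated, so this is an assumption), 80% power, 1:1 allocation, no continuity correction:

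n per group = [1.96·√(2p̄(1−p̄)) + 0.84·√(p₁(1−p₁)+p₂(1−p₂))]² / (p₁−p₂)²

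- 40% vs 10%: 31.5, so 32 (stated 32).
- 30% vs 10%: 61.6, so 62 (stated 64; power at 64 per group is 81.5%).

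The stated sizes reproduce from a 10% control rate.

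**2. Make-up of the comparator.** LAA share in Table 3: 11/(11+21+10) = 11/42 = 0.262. Scaled to 300 patients:

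- cryptogenic 300×32/79 = 122
- CE+SVD 300×31/79 = 118
- LAA 300×11/79 = 42
- pooled comparator 118+42 = 160

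No loss to poor image quality is deducted.

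**3. Pooled rate and power.** The article gives no LAA or CE/SVD prevalence, so both are assumed.

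Pooled rate = 0.262·p(LAA) + 0.738·p(CE/SVD)

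Power = Φ{(|p₁−p₂| − 1.96·s₀)/s₁}, where s₀ is the standard error under a common rate and s₁ the standard error under the two separate rates.

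Example with CE/SVD 10%, LAA 40% and cryptogenic 30%:

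- pooled rate 0.262×0.40 + 0.738×0.10 = 0.179
- s₀ = 0.0507, s₁ = 0.0514
- (0.1214 − 0.0993)/0.0514 = 0.43, so power is 67%

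With CE/SVD at 10% and 122 vs 160 patients:

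| LAA assumed | Pooled rate | Difference from 30% | Power at 30% | Difference from 40% | Power at 40% |
|---|---|---|---|---|---|
| 20% | 12.6% | 17.4 points | 95% | 27.4 points | >99% |
| 30% | 15.2% | 14.8 points | 84% | 24.8 points | >99% |
| 40% | 17.9% | 12.1 points | 67% | 22.1 points | 98% |
| 50% | 20.5% | 9.5 points | 45% | 19.5 points | 95% |
| 60% | 23.1% | 6.9 points | 26% | 16.9 points | 86% |

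Cryptogenic vs CE+SVD only (122 vs 118) at 30% vs 10%: about 98% power and a 20-point difference (30 points at 40%).

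With CE/SVD at 3% and cryptogenic at 30%, the pooled test has 99, 94 and 84% power for LAA at 30, 40 and 50%.

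**4. Dependence on case mix.** Hold LAA at 40% and CE/SVD at 5% (illustrative):

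- LAA share 10%: 0.10×40 + 0.90×5 = 8.5%
- LAA share 40%: 0.40×40 + 0.60×5 = 19%

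The comparator rate more than doubles with no change in any subtype.

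**5. Can 10% be the pooled rate?** At the Table 3 mix, p(CE/SVD) = (0.10 − 0.262·p(LAA))/0.738:

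- LAA 20%: CE/SVD 6.5%
- LAA 30%: CE/SVD 2.9%
- LAA 37%: CE/SVD 0.4%
- LAA 40%: negative, so impossible

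The ceiling is 0.10/0.262 = 38%. A pooled 10% is therefore possible, but only if the positive control lies below the 40% planned for cryptogenic stroke.

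**The case against.** A reader might infer that the 10% and the 64 per group do not apply to the test that will be run. The documents do not support this. The Sample size section attaches the 10% to defined etiology, the same label as the test, and 32 and about 62 follow from it. A mismatch needs a combination that the article never states: a 10% rate taken from CE/SVD alone, with a pooled test.

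Nor can the 10% be called impossible as a pooled rate. That requires an LAA prevalence of about 38% or more, and none is given. LAA at 30% with CE/SVD at about 3% pools to 10%, and LAA would still be a working positive control. The pilot data behind the 10% are unpublished and their subtype mix is not stated. The 26% LAA share rests on 42 patients (95% Wilson interval 15 to 41%). All of this stands.

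It is also true that the consequence is bounded. The prevalence estimate in cryptogenic stroke and the McNemar comparison of sides do not use the control group. If LAA has the higher prevalence, as its role implies, pooling works against the hypothesis and not for it. The 300 patients give groups well above 64.

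One could add that a condensed article may leave the choice of subtypes to the full protocol or analysis plan. This carries less weight. The article itself assigns the control roles, names the comparison and names the test, and these statements do not fit together.

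**Conclusion.** The point holds as a badly fixed comparator, not as a proven sample-size error. As written, the positive control is pooled with the negative controls, which dilutes the contrast and makes it depend on the LAA share.

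The loss can only be given as a range. It assumes a two-sided test, the interim mix carried to 300 patients and no image-quality losses. With CE/SVD at 10% and cryptogenic at 30%, power falls from about 98% to between 95 and 45% for LAA between 20 and 50%. With CE/SVD at 3% it stays at 84% or more over that range. At the plan's 40% for cryptogenic stroke it is at least 86% for LAA up to 60% (CE/SVD 10%), and the cost is mainly a difference that shrinks from 30 points to as little as 17.

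Whether the 10% is the pooled rate or the CE/SVD rate remains unclear.

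**What to change.** In Primary outcome and in Imaging and statistical analysis, define the between-group comparison as cryptogenic stroke versus CE+SVD. Report LAA separately as the positive control, with its prevalence and confidence interval. In Sample size, state which subtypes the 10% covers.

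This follows the roles already assigned under Patient population and needs wording only. The cost is that about 42 LAA patients leave the comparator. About 118 CE+SVD patients remain, above the 64 planned. The change should be recorded before the final analysis, because the Discussion already reports an initial look at primary endpoint data (the comparison of sides), and a comparator chosen later could be challenged as data-driven.
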